## Abstract

**Objective::**

To explore the effect of modular transitional nursing intervention on the improvement of self-management of the patients with cancer pain.

**Method::**

This study will be conducted from March 2021 to May 2022 at Affiliated Hospital of Beihua University. The experiment was granted through the Research Ethics Committee of Affiliated Hospital of Beihua University (4348–019). Eighty patients are analyzed in our study. The patients will be included if they are between 18 and 70 years old and are diagnosed with cancer, the pain intensity score on moderate level, the pain lasts for more than 3 days, and the patients who have signed the written informed consent. While the patients will be excluded if they have a documented history of drug or alcohol abuse, and patients with limited performance, and patients have a surgery in the past 3 days. The primary result mainly expresses as intergroup differences in self-management disorders (Barriers Questionnaire-II) associated with the cancer pain. And the secondary results include the quality of life (QOL) and pain intensity. All the analyses are implemented with SPSS for Windows Version 20.0.

**Results::**

Table 1

**Table 1 T1:** Outcome measures after modular transitional nursing intervention.

Variables	Nursing group (n = 40)	Control group (n = 40)	*P* value
Pain intensity (average)			
Pain intensity (maximum)			
Knowledge cancer pain			
Cognitive barriers			
Function			
Physical			
Role			
Emotional			
Cognitive			
Social			

will show the clinical outcomes between the 2 groups.

**Conclusion::**

A modular transitional nursing intervention appears to reduce pain in cancer patients.

**Trial registration number::**

researchregistry6262.

## Introduction

1

Many cancer patients suffer from a variety of symptoms, which can affect their social and physical functioning.^[1,2]^ For the cancer patients, pain is one of the most burdensome and feared physical symptoms.^[3,4]^ A recent study indicated that in the cancer patients, the incidence of pain remains high: 64 percent in those with terminal, advanced and metastatic disease, and 59 percent in those receiving anti-cancer treatment.^[5]^ The nurses and physicians are involved in the management of daily cancer pain, but they often fail to detect and treat the syndromes of pain.^[6,7]^ The factors associated with the ineffective pain management can be divided into 3 categories, namely, patients, healthcare providers and healthcare system. In the healthcare system, “curing” is more concerned than “caring” for cancer patients, including the management of symptom. Health care providers often lack the knowledge and attention about the management of pain and patients are unwilling to report pain to physician. Fear of drug resistance, drug addiction and worry about the side effects can also affect their intake of painkillers. Despite pain education programs have increased the knowledge of nurse and patient in the management of pain, none of these programs, as far as we know, has improved the pain results.^[8–10]^ Goldberg et al^[11]^ have explored the educational effects of nurses on topics related to pain. Nevertheless, these interventions did not result in any obvious reduction in patients pain severity.

There is increasing evidence of the importance of transitional nursing interventions, nevertheless, the influence of educational interventions that utilize transition preparation for the patients with cancer pain during hospitalization has not been recognized. Hence, the purpose of our investigation is to assess the influence of Self Care Improvement through Oncology Nursing to reduce patients barriers and improve pain management in cancer patients.

## Methods

2

This study will be conducted from March 2021 to May 2022 at Affiliated Hospital of Beihua University. The experiment was granted through the Research Ethics Committee of Affiliated Hospital of Beihua University (4348–019) and recorded in research registry (researchregistry6262). Sequence of random numbers is generated by a computer. Sequentially numbered sealed opaque envelopes are used for the concealment of random numbers. All the patients taking part in our experiment are randomly divided into control and study group and each group includes 40 patients.

### Inclusion and exclusion criteria

2.1

The patients will be included if they are between 18 and 70 years old and are diagnosed with cancer, the pain intensity score on moderate level, the pain lasts for more than 3 days, and the patients who have signed the written informed consent. While the patients will be excluded if they have a documented history of drug or alcohol abuse, and patients with limited performance, and patients have a surgery in the past 3 days.

### Intervention

2.2

In intervention group, Self Care Improvement through Oncology Nursing program is managed through the specially trained nurses. The counseling courses are divided into 3 modules. The first module, namely, pharmacologic management of pain, introduces a reliable pain evaluation, the use of the pain medications, and the communication about patient pain. The second module, namely the non-pharmacologic management of pain, contains the information about the influence of adjuvant pain managements and gives the patient a CD instructing them to independently perform the progressive muscle relaxation. While the third module (namely the discharge management related to pain) is designed to help the patients cope properly with potential self-management issues associated with pain in the process of transition to the outpatient care. Advice is provided on how to adhere to the self-management methods learned in the first and second modules after discharge. The checklist is provided to ensure appropriate discharge management is implemented. At the aim of ensuring that the consultation is tailored to the personal needs, but standardized in accordance with basic model, we offer an evaluation of the patients skills, knowledge, perceptions and attitudes of resources, and provide the indicative questions. Each question is associated with the intervention, for instance, offer the information on the types of application and the plans of pain medication. In control group, the patients are given care as usual, involving the standard pharmacological treatment of pain, but there is no standardized written material and teaching application, nor other evidence-based management options.

### Outcomes

2.3

The primary result mainly expresses as intergroup differences in self-management disorders (Barriers Questionnaire-II)^[12]^ associated with the cancer pain. And the secondary results include the quality of life (QOL) and pain intensity.

### Statistical analysis

2.4

Through utilizing the software of IBM SPSS Statistics for Windows, version 20.0, all the data can be analyzed (IBM Corp., Armonk, NY, USA). Afterwards, all the data are described with appropriate characteristics such as mean, median, standard deviation as well as percentage. The qualitative parameters for the groups are evaluated by *t* test. The categorical variables are determined by the χ^2^ tests. When *P* is less than .05, it is viewed to be significant in statistics.

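### The scores are to be compared by an unadjusted t test on post-intervention values; adjusting for baseline would be more precise, modestly for pain and, given a baseline Barriers Questionnaire-II score, more for the primary outcome

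*Protocol article*

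**What the plan says.** All references are to the protocol article.

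- **Test.** The Statistical analysis section states "The qualitative parameters for the groups are evaluated by" a t test and assigns chi-square tests to categorical variables, with significance at P below .05. The word for the first type of variable must mean quantitative, since categorical variables are dealt with separately. No covariate, change score or baseline term is named.
- **What is compared.** The Table 1 shell is titled "Outcome measures after modular transitional nursing intervention". It has one column per arm and one P value for average and maximum pain, knowledge, cognitive barriers and the function scales. It has no baseline or change row.
- **Baseline pain.** The entry criteria include "the pain intensity score on moderate level", so each patient's pain must be rated before enrolment.
- **Outcomes.** The Outcomes section makes BQ-II primary and adds: "And the secondary results include the quality of life (QOL) and pain intensity". It does not say whether BQ-II or quality of life is measured at baseline.
- **Size and allocation.** Patients "are randomly divided into control and study group and each group includes 40 patients", using a computer-generated sequence. Stratification is not mentioned.

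**The concern.** A t test on follow-up scores ignores what is known about each patient before randomisation. Two things are lost.

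The first is precision. Variation between patients that a baseline score could explain stays in the error term, so the confidence interval is wider and the power lower than 80 patients could give.

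The second is protection against an unlucky draw. If one arm happens to start with worse scores, part of that difference appears in the estimated effect.

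Both matter more in a small trial. The article gives no power calculation that would show there is precision to spare. For pain, a pre-treatment score is taken anyway.

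**Working it through.** The article states no effect size, SD, power or correlation, so it has no figure to reproduce.

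**Inputs from the article:** 40 per arm; significance level .05. The article does not state whether tests are two-sided; two-sided is assumed.

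**Further assumptions:** a true effect of 0.5 SD for illustration, and a baseline-outcome correlation r shown over a range.

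**1. Unadjusted comparison.** The standard error in SD units is sqrt(2/40) = 0.224. With the noncentral t distribution on 78 degrees of freedom, power at 0.5 SD is 59.8%. The difference detectable with 80% power is 0.634 SD.

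**2. Chance imbalance.** Under simple randomisation, the difference in baseline means has the same SD, sqrt(2/40) = 0.224, with a 95% range of about ±1.96 × 0.224 = ±0.44 SD. It exceeds 0.25 SD in either direction in about 26% of trials of this size. The part that reaches the unadjusted estimate is r × imbalance. For an imbalance of 0.25 SD this is 0.25 × 0.2 = 0.05 SD at r = 0.2 and 0.25 × 0.5 = 0.125 SD at r = 0.5.

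**3. ANCOVA.** The residual variance is (1 − r²) times the unadjusted variance, the equivalent unadjusted sample size is 80/(1 − r²), and 77 degrees of freedom remain.

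| Assumed r | Variance ratio | Equivalent patients | Power at 0.5 SD | Detectable at 80% power |
|---|---|---|---|---|
| none (t test) | 1.00 | 80 | 59.8% | 0.634 SD |
| 0.3 | 0.91 | 88 | 63.9% | 0.605 SD |
| 0.5 | 0.75 | 107 | 72.2% | 0.549 SD |
| 0.6 | 0.64 | 125 | 78.8% | 0.508 SD |

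**4. Pain: effect of the entry restriction.** Admitting only moderate pain narrows the spread of baseline pain and so lowers r. Let u be the ratio of restricted to unrestricted baseline SD. Then r' = r·u / sqrt(1 − r² + r²u²). For an unrestricted r of 0.5:

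- u = 0.4: r' = 0.20 / sqrt(0.75 + 0.04) = 0.225, variance ratio 0.949.
- u = 0.6: r' = 0.30 / sqrt(0.75 + 0.09) = 0.327, variance ratio 0.893.

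The variance therefore falls by about 5% to 11%. If the unrestricted r were 0.7, r' would be about 0.37 to 0.51 and the fall about 13% to 26%. The values of u are assumptions too.

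**5. BQ-II and quality of life.** The pain restriction does not act directly on these scores, so the r = 0.5 row is a reasonable illustration, but only if a baseline of the same instrument exists in both arms. The one assessment of related content that the article describes is in the Intervention section, "we offer an evaluation of the patients skills, knowledge, perceptions and attitudes of resources". It serves to tailor the counselling in the intervention arm and is not presented as an outcome measurement. It could not be a two-arm baseline, and it does not show whether BQ-II is taken at baseline.

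**The case against.** The strongest reply is that the stated method is sound. Under randomisation the t test is unbiased and keeps its type I error, and its standard error already allows for chance imbalance. **This stands.** A reader might infer from the talk of imbalance that the planned P values are wrong or the estimate biased; neither follows. The imbalance matters only conditionally, for the particular allocation that occurs.

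A second reply is that the pain score already in hand does not serve the primary outcome. **This also stands.** A reader might infer that a covariate for BQ-II is lying unused. The article documents none, and baseline pain may predict BQ-II only weakly. Nor does the article show that a baseline BQ-II is missing: a condensed article can leave the assessment schedule to the full protocol.

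Third, the entry pain score is a single unspecified rating, whereas Table 1 has average and maximum pain. It may match neither exactly, and it may be recorded as a category. **This limits the gain for pain** and the claim that adjustment there is free.

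Fourth, adjustment might be set out in an analysis plan that is not shown. **This carries less weight.** The article names its test and prints its table shell, so the unadjusted comparison is a stated choice and not merely an omitted detail.

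**Conclusion.** The point holds as a recommendation on efficiency, not as an error that invalidates the trial. The article chooses an unadjusted t test and a table of post-intervention values while requiring a pain score at entry.

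- **Pain (secondary):** the gain is probably modest, about 5% to 11% lower variance. This rests on an assumed unrestricted r of 0.5 and an assumed narrowing of baseline SD to 0.4 to 0.6 of its full value.
- **BQ-II (primary) and quality of life:** the gain is potentially worthwhile, with power rising from 60% to 72% at an assumed 0.5 SD effect and r = 0.5. It depends on a baseline completed in both arms, which the article neither describes nor rules out.

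The equivalent sample sizes of 107 and 125 patients at r of 0.5 and 0.6 should not be read as applying to pain, where the entry rule makes lower correlations likely.

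**What to change.** 1. Replace the t test for each score by ANCOVA: follow-up score on group plus that outcome's baseline score. Report the adjusted mean difference with its 95% confidence interval. Make the ANCOVA of BQ-II the primary analysis and keep the unadjusted t test as a sensitivity analysis.
2. For BQ-II and quality of life, use a baseline completed by all 80 patients before the allocation envelope is opened. If it is already planned, say so. If not, add it before enrolment, because a missed baseline cannot be recovered.
3. For pain intensity, use the entry score as covariate. State which scale and recall period it uses, that it is recorded as a number, and how it relates to average and maximum pain.
4. Add baseline columns and the adjusted difference to the Table 1 shell, and correct the wording so that the sentence on the t test refers to quantitative variables.

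The cost is small: at most one extra completion of the same forms per patient. For pain, a score is already taken. The named software, SPSS version 20, fits the model.

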## Result

3

Table 1 will show the clinical outcomes between the 2 groups.

## Discussion

4

Our experiment is the first to explore the effects of modular transitional nursing intervention to improve the management of pain and decrease patient barriers for the cancer patients. Pain remains one of the most painful and prevalent symptoms in the cancer patients, especially in the end-stage of this disease.^[13,14]^ Fourty percentage of patients with the early cancer or intermediate cancer and 90 percent of patients with the advanced cancer suffer from moderate to severe pain, and approximately 70 percent of cancer pain patients do not get enough pain relief.^[15]^ The pain associated with cancer is a main healthcare challenge.^[16]^ Despite the use of strong opioids may be appropriate for the survivors of moderate to severe pain, most of the cancer survivors do not need them for their pain problems. Furthermore, as more than 40 percent of the cancer survivors live more than 10 years, there is an increasing concern about the opioids long-term side effects and the risks of overdose, abuse, and misuse in the cancer survivors.^[17,18]^ Studies have indicated that the inadequate exchange of information between health care providers, the lack of communication with the patients and their family members in the transition period, and the high incidence of post-hospital adverse events suggest that the inadequate nursing transition from the hospital to family is frequent. Thus, we conduct this investigation to explore the effect of modular transitional nursing intervention on the improvement of self-management of the patients with cancer pain.

## Conclusion

5

A modular transitional nursing intervention appears to reduce pain in cancer patients.
